##### Qualitative data

2.9.2.6

We will conduct qualitative focus groups and interviews with study participants to evaluate their experiences and perceptions of participating in an intervention study. These data are collected after the final session for both groups (i.e., post-intervention only).

#### Additional outcome measures

2.9.3

##### Body composition

2.9.3.1

Body composition, specifically body fat, is thought to be a determinant of autonomic nervous system activity (Poliakova et al., 2012; Triggiani et al., 2019). It is plausible that yoga may favorably modify body composition, and thereby introduce a potentially confounding variable. Accordingly, a physician’s digital scale, stadiometer, and dual energy x-ray absorptiometry (Hologic, Discovery W, QDR Series, Bedford, Massachusetts, United States) are used, as previously described (Ryan et al., 2020; Williams et al., 2021), to quantify changes in body mass, body mass index, and body composition.

### Data collection

2.10

Primary and secondary outcome data are acquired during pre-intervention and post-intervention assessment visits, as outlined in earlier sections and Figure 1. To ensure quality of data acquisition, the following procedures were completed prior to participant enrollment. For NIH Toolbox data acquisition, the study PI and other assessors watched training videos, carefully reviewed the NIH Toolbox manual, and practiced administering the assessments. The study PI also trained assessors on fNIRS and force plate data acquisition, which included watching video tutorials, completing trial runs of procedures, and checking data quality of trial runs. For data acquisition related to evaluating ANS function, the study PI works closely with a co-investigator, who has expertise in HRV data acquisition and analysis (Williams et al., 2021); this co-investigator trained research team members who acquired pre-intervention and post-intervention ECG data. Additionally, the study PI communicated with Polar representatives and technical support personnel to confirm procedures for within-session data acquisition using Polar devices. Finally, study co-investigators have significant expertise in fMRI acquisition methods (Burzynska et al., 2013; Thomas et al., 2013, 2022; Mendez Colmenares et al., 2023) which supported appropriate selection of MRI sequences as outcomes; parameters for these sequences were also confirmed with an established MRI technician prior to any data acquisition.

### Data management

2.11

All data are indexed using participant IDs to promote confidentiality, although the study PI has a list that links study ID to participant names. This list is on a password protected spreadsheet and saved to the PI’s personal network drive on a password protected computer. Raw data for all outcome measures are saved on university network drives, which are regularly backed-up by the IT department. Scored or summarized data are also stored within a Microsoft Access database which is managed by the study PI and the project manager. This database is also located on a university network drive. Most data can be imported into the Microsoft Access database directly from the acquisition program, which reduces the possibility of human error in data entry. Manual data entry is completed by a trained research assistant for participant demographic information including age, sex, race and ethnicity, type of ABI, time since injury, self-reported balance limitation, prescription medication use, and handedness. These data are reviewed by the study PI to ensure accuracy.

### Data monitoring

2.12

The size of the study and associated budget did not support creation of a data monitoring committee. In addition to careful monitoring of possible adverse events during each yoga or exercise sessions, the study PI is responsible for evaluating all outcome data following post-intervention visits of the first cohort to assess if there are any significant safety concerns or poor outcomes that warrant termination of the trial.

#### Harms

2.12.1

During each yoga or exercise session, interventionists are checking for and reporting any adverse events that happen before, during, or after the sessions. Interventionists have been provided a formal adverse events reporting form, which includes instructions on when to contact the Co-PI, PI, or – in extreme and unlikely circumstances – emergency services.

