### Selection of subjects

2.2

Participants are included if they are at least 18 years old, have sustained an ABI at least 6 months before start of study (operationally defined by our team as “chronic”), and have a self-reported balance impairment of moderate or greater, via the Neurobehavioral Symptom Inventory balance item (King et al., 2012). If completing magnetic resonance imaging (MRI) assessments, participants must meet standard screening criteria for a 3 Tesla scanner. To support successful recruitment, participants are not required to be yoga or exercise naïve, as the research was conducted in a relatively small community. Participants are excluded if they have not sustained an acquired brain injury or if they sustained an acquired brain injury within the past 6 months. They are also excluded if they self-report a mild balance impairment or no balance impairment, again via the neurobehavioral symptom inventory (King et al., 2012). The interventionists leading the yoga and low-impact exercise sessions were required to be a certified yoga instructor or personal trainer, respectively. Both interventionists had to be willing to follow a standardized protocol, designed by the co-principal investigators (Co-PIs), and complete human subjects training. Additionally, both interventionists were trained by occupational therapists on appropriate ways to communicate with and physically support individuals with brain injury during yoga and exercise.

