### Masking

2.7

For practical purposes, any research team member who provides or supports the interventions, including the Co-PI, are unmasked. Research team members who conduct pre-and post-intervention assessments, including the study PI, are masked to group assignment with one exception. Research team members who assess anatomy or physiology with instruments like MRI are not necessarily masked, as their knowledge of group membership is unlikely to influence outcomes. These individuals are not involved in data analysis where bias could be introduced. The study PI will only become unmasked in the instance of an adverse event, if the Co-PI is unable to share adequate details with the research compliance office (highly unlikely). Otherwise, the study PI will become unmasked after post-intervention assessments are completed and scored.

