#### Additional procedures for both interventions

2.8.3

All participants are informed that they can discontinue yoga or low-impact exercise at any time. In prior work (Stephens et al., 2020, 2022), there have been no adverse effects from yoga, but the research team is carefully monitoring participants at each yoga or exercise session for any adverse event, such as falls, fainting episodes, or significant discomfort. As noted, both interventions have manualized protocols to guide sessions to ensure adherence to the protocols. Additionally, adherence is being monitored for each yoga and exercise sessions with fidelity checklists. The Co-PI, who is not a masked assessor, reviews checklists throughout the intervention period, and – if necessary – meeting with interventionists to improve protocol adherence. Fidelity metrics are also being tracked for both interventions and will be reported with study outcomes. Finally, because participants are in a chronic phase of acquired brain injury recovery, they are rarely receiving concomitant care or other interventions. However, participants are asked to disclose concomitant care, interventions, or exercise protocols they might be following during the intervention period, but they are not prohibited from continuing with these activities.

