##### Standing balance

2.9.1.1

Balance performance is assessed using two methods:Balance is first assessed using a validated measure (Peller et al., 2023), the National Institutes of Health (NIH) Toolbox Standing Balance Task. This measure is administered using the NIH Toolbox app on an iPad (version 9) and the Balance Pod app on an iPhone (version 6), which are paired via Bluetooth. Prior to data acquisition, the study PI places a gait belt on the participant and secures the iPhone to the gait belt using a cellphone armband that is affixed to the gait belt. The Balance Pod app, via the iPhone, measures anterior–posterior sway during balance tasks which include: bipedal standing on a hard surface with eyes open; bipedal standing on a hard surface with eyes closed; bipedal standing on a soft surface (foam pad) with eyes open; bipedal standing on a soft surface with eyes closed; and tandem standing on a hard surface with eyes open. For all balance tasks, participants must remove their shoes and place their feet together with their heels and balls of feet touching. For eyes-open tasks, participants are instructed to fixate on an ‘X’ which is placed on wall in front of them at shoulder height. Tasks are administered in order of difficulty, starting with the easiest task (bipedal standing on a hard surface with eyes open). Each task lasts 50 s and can be repeated once if the participant has loss of balance (LOB) and steps out of the position. For safety purposes, participants complete all balance tasks in a corner, so they have walls on two sides if LOB occurs. The study PI also stands on their other side to stabilize participants in case of LOB. Only participants who make it to the fifth (and hardest task) complete the second balance assessment method.Balance performance is also assessed using a previously validated (O'Connor et al., 2016; Goble et al., 2018; Richmond et al., 2018) force plate (Balance Tracking Systems, Inc., San Diego, CA) during simultaneous neuroimaging assessment with functional near-infrared spectroscopy (fNIRS). Four balance tasks are administered and include: bipedal standing on a hard surface with eyes open; bipedal standing on a hard surface with eyes closed; bipedal standing on a soft surface (foam pad) with eyes open; and bipedal standing on a soft surface with eyes closed. Each task is 30 s in duration, and tasks are repeated four times for a total of 16 trials, as task repetition is necessary to generate an averaged brain response. Balance performance for each trial is acquired with a sampling frequency of 25 Hz, and postural stability is quantified by measuring total center of pressure (COP) length, anterior–posterior COP length, and medio-lateral COP length. Again, for safety purposes, all balance trials are completed in a corner, and the study PI stands near the participant to stabilize them in instances of LOB. A masked study team member documents all instances of LOB during trials.

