### Consent

3.3

Written informed consent is acquired by the study PI and Co-PI from participants or their legal power of attorney. This study includes two consent forms (see appendices) – one for the main study and one specific to MRI procedures (this is only acquired from participants who are eligible for MRI). Consent is acquired during a pre-intervention assessment visit, which occurs after participants are screened for eligibility. To note, if participants are deemed ineligible for the study during screening, the research team retains none of their information, with the exception of their initial email correspondence for recruitment tracking. Written informed consent procedures include the following steps: (1) Participants are emailed consent form(s) in advance of their pre-intervention assessment visit. (2) Upon arrival at the pre-intervention assessment visit, participants review a printed copy of the consent form(s) with the PI or Co-PI, who clarify procedures and answer questions. (3) After questions are addressed, participants initial and sign consent form(s) and the PI or Co-PI also signs the form(s). All participants are offered a copy of the signed consent form at this time. (4) Throughout the study, participants are reminded that they can decline to complete any procedures, which has no penalty except possible removal from the study.

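### Adverse events are checked at class sessions by unmasked, arm-specific instructors; with no uniform harms inquiry described beyond the classes, events may be under-recorded and counts may depend on the reporter

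*Protocol article*

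**What the plan says.** Harms (2.12.1) sets the collection rule: at each class, "interventionists are checking for and reporting any adverse events that happen before, during, or after the sessions". It adds that "Interventionists have been provided a formal adverse events reporting form", with instructions on when to contact the Co-PI, the PI or emergency services. Section 2.8.3 is also tied to the class: "the research team is carefully monitoring participants at each yoga or exercise session for any adverse event, such as falls, fainting episodes, or significant discomfort". Data monitoring (2.12) again speaks of monitoring during sessions. It states that there is no monitoring committee and makes the PI responsible for reviewing outcome data after the first cohort, for safety among other things.

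The reporters differ by arm. Under Selection of subjects (2.2) the session leaders were "required to be a certified yoga instructor or personal trainer, respectively". Under Masking (2.7), "any research team member who provides or supports the interventions, including the Co-PI, are unmasked".

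Other sections describe contacts and records that could reveal a harm:
- Participant retention (2.4): anyone who misses a class is contacted and the reason is noted. Post-intervention visits are planned for everyone who takes part in sessions.
- Standing balance (2.9.1.1), on the force-plate test: "A masked study team member documents all instances of LOB during trials".
- Consent (3.3): participants are told that "they can decline to complete any procedures, which has no penalty except possible removal from the study".

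**The concern.** The article gives fall risk as a main reason for the trial and lists falls and fainting among the events to watch for. Yet the adverse event procedure runs through the class and the person leading it. A participant who falls during a balance test, in the fortnight after the last class, or after giving up the programme does not clearly meet anyone whose described task is to ask about harms and complete the form.

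Two things are at stake. First, a low count of harms could reflect how events were sought rather than how safe the programmes are. The only planned safety review, by the PI after the first cohort, would draw partly on these records. Second, all class-based reporting in one arm passes through a yoga instructor and in the other through a personal trainer, each aware of the programme being delivered. If one of them asks more often or has a lower threshold for reporting, the recorded counts will differ without any difference in harm.

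**Working it through.** The protocol states no adverse event rate and plans no comparison of harms, so there is no figure to reproduce. The check sets the sections side by side, then adds simple arithmetic.

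**1. Coverage by setting**

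| Setting | What is described | Described as a harms inquiry? |
|---|---|---|
| During class | Interventionists check and report; form provided (2.12.1, 2.8.3) | Yes |
| Between classes | Can be reported at the next class, since before and after carry no time limit (2.12.1) | Possibly; no set question described |
| Toolbox balance test | Gait belt, corner position, PI beside the participant; one repeat allowed after loss of balance (2.9.1.1) | No; no log or form described |
| Force-plate test | Corner position, PI nearby, every loss of balance documented (2.9.1.1) | No; log not linked to the form |
| After the last class | Post-intervention visit within 2 weeks (2.9.1) | No |
| Missed class or stopping | Contact after a missed class, reason recorded (2.4) | No; described under retention |
| Randomised, never attends | Post-intervention visit is stated for those who take part in sessions (2.4) | No |

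Only participants who reach the fifth Toolbox task go on to the force plate. The least steady participants therefore do only the test for which no loss-of-balance log is described.

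**2. Timeline**

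Inputs: pre-intervention visit 2–3 weeks before the first class, and post-intervention visit within 2 weeks of the last (2.9.1); 8 weeks of classes (2.8).
- Visit to visit: shortest 2 + 8 + 0 = 10 weeks; longest 3 + 8 + 2 = 13 weeks.
- Weeks with no class: shortest 2 + 0 = 2; longest 3 + 2 = 5.
- An event in the 2–3 weeks before the first class can still be reported at that class. An event in the 0–2 weeks after the last class has no later class at which to be reported.

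**3. What unequal detection could do (assumed values)**

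Planned enrolment is 36 (2.5), so 18 per arm at 1:1. Expected recorded events = n × true risk × detection probability. Take the same true risk in both arms:

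| True risk | Detection 90% vs 60% | Detection 80% vs 50% |
|---|---|---|
| 10% | 1.62 vs 1.08 | 1.44 vs 0.90 |
| 20% | 3.24 vs 2.16 | 2.88 vs 1.80 |
| 30% | 4.86 vs 3.24 | 4.32 vs 2.70 |

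The spurious ratio is 0.9/0.6 = 1.5 or 0.8/0.5 = 1.6. With equal detection it is 1.0. Nothing in the article says what detection is in either arm.

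**4. What zero recorded events would show**

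With no recorded event among 18 people, the one-sided 95% upper limit for the risk of a recorded event is 1 − 0.05^(1/18) = 15.3%. If a fraction d of affected people is recorded, the limit for the true risk is 15.3%/d: 17.0% at d = 0.9 and 25.6% at d = 0.6 (d is assumed).

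**The case against.** The strongest reply is that the plan covers more than a quick reading suggests, and much of that reply stands.

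- A reader might infer that only the class hours are covered, so that falls at home go unrecorded. The wording does not support this. It sets no time limit on before or after, and with two classes a week a fall at home can be reported within days. For the same reason, class hours as a share of all hours is not a measure of coverage.
- A reader might infer that falls at the balance tests are lost. Both tests are supervised by the PI, who also carries the safety review, and loss of balance at the force plate is logged. What is unstated is the link from these observations to the adverse event form. Nor does every participant do the force-plate trials.
- Group assignment is revealed at the end of the pre-intervention visit, so an event during testing at that visit cannot be a harm of either programme.
- People who miss classes are contacted, and poor attenders still have a post-intervention visit. Removal after declining a procedure is only possible, not automatic.
- A reader might infer that harms cannot be compared between arms. That is not shown. The session schedules are equal, the form is described without any difference by arm, the wider research team is also said to monitor sessions, and no between-arm test of harms is planned.
- How the team's previous studies collected adverse events is not stated, so their reports of no adverse effects cannot be criticised on that ground.

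The article is also a condensed account, and the form itself is not shown; it may contain prompts that cannot be seen here. This excuses missing detail. It does less to excuse the rule, which three sections state in the same session-based way in an article that sets out to describe every component of the protocol.

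**Conclusion.** The point holds as a weakness in how harms are sought. The described route is a session-based check by unmasked instructors who differ by arm. The other contacts may bring events to light, but none is described as a uniform harms inquiry. Under-recording is therefore possible, most plausibly at assessment visits, in the 0–2 weeks after the last class, and in people who stop. A difference in recorded counts produced by the reporters is also possible.

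The size cannot be determined from the document. Under the assumed detection rates, the distortion is about one event in an arm of 18 at a true risk of 20%. That is small in absolute terms, but it is a ratio of 1.5 where none exists. Neither missed events nor a bias between arms is demonstrated. The primary analyses of balance and heart rate variability are unaffected. The change is worth making because it is cheap and because, with no monitoring committee, these records are a main source of safety information.

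**What to change.** Amend section 2.12.1 as follows.

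- **One question for everyone.** From the pre-intervention to the post-intervention visit, ask every randomised participant in both arms the same scripted question: any fall, faint or injury since last asked.
- **Existing channel.** Send it with the text messages already used for appointment reminders. People who have stopped classes no longer have class reminders, so send a few added messages to those who consent to further contact.
- **Masking kept.** Have the project manager, who prepares the allocation envelopes and so knows the assignments, log replies on the existing form. Assessors then do not see them.
- **Assessment visits.** Use the same form for any fall or injury at either visit, including during the Toolbox test.
- **Reporting.** Report events by arm for all randomised participants, separating in-class, out-of-class and pre-allocation events. If the first cohort (12 people) was followed under the present rule, show harms by cohort as well, so that the two methods of collection are not mixed.

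The cost is modest logging work, a few extra messages and a short IRB amendment. The drawback is that more background falls will be recorded in both arms; reporting in-class and out-of-class events separately makes these easier to interpret.

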#### Auditing

2.12.2

The size of the study and associated budget did not support creation of a formal auditing procedure. However, it is important to note that the funder is not involved in any aspect of data acquisition, interpretation, or dissemination of findings.

### Statistical analysis of primary outcomes

2.13

#### Balance data

2.13.1

T-Scores from the NIH Toolbox Standing Balance Task and center of pressure metrics from the force plate will use mixed effects statistical model to assess prospective within-subject (factor of time) and between-group (yoga vs. control) differences in balance performance.

#### HRV data

2.13.2

There are multiple HRV metrics (e.g., time-series and frequency-band values) calculated within Kubios (Tarvainen et al., 2014). However, a review study showed consistent stabilization of the low frequency (LF) band power after yoga, reflecting an improved equilibrium of parasympathetic and sympathetic activity, (Zou et al., 2018) so initial analyses will use mixed effects statistical model to assess prospective within-subject (factor of time) and between group (yoga vs. control) differences in LF band power data.

### Statistical analysis of secondary outcomes

2.14

#### Functional connectivity data

2.14.1

This analysis plan will be guided by findings from behavioral data and completed in SPM 12, using false discovery rate (FDR) corrected contrasts to evaluate potential within and between-group differences, along with interaction effects, in intrinsic functional connectivity of specific neural networks (e.g., motor network).

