##### Region of interest analysis

2.9.2.2

To evaluate potential differences in specific WM tracts, we first estimate myelin content in the entire WM by averaging the MWF values from the entire skeleton for each participant (whole WM). Next, we extract mean MWF values from regions representing the major association, projection, and commissural fibers, as described previously (Burzynska et al., 2013), using the diffusion tensor imaging (DTI) white-matter atlas (Mori et al., 2005), with the aim to include the core regions specific to each tract. The corpus callosum is segmented so that genu represents prefrontal commissural fibers, body containing premotor, supplementary motor, motor and sensory fibers, and splenium containing parietal, temporal and occipital connections (Hofer and Frahm, 2006). The prefrontal WM region is defined as y > 12 in MNI coordinate space and whole WM included the whole TBSS skeleton. The cingulum includes both the ventral and dorsal segments, and the corticospinal tract is represented by the core regions of the superior corona radiata, posterior limb of the internal capsule, and the cerebral peduncles. The uncinate is probed in the lateral ventral prefrontal region as well as in the section along the fronto-occipital fasciculus. Mean MWF are extracted from each region using fslmeans in FSL.

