#### Structural integrity

2.14.2

This analysis plan will also be guided by findings from behavioral data using contrasts to evaluate within and between-group differences, along with interaction effects, in structural integrity of specific WM tracts.

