#### Secondary outcomes

4.1.2

There is limited research on yoga on for brain injury, especially regarding its impact on the integrity neural networks and task-dependent brain activity. However, there is evidence from healthy populations and pilot data from our lab to inform our hypotheses. Specifically, in healthy individuals yoga can enhance structure and function of brain regions and neural networks, such as the default mode network (Gothe et al., 2019). Additionally, in adults with chronic acquired brain injury, pilot data from our lab suggests improved neural efficiency during balance tasks (Stephens et al., 2023). Based on these findings, we hypothesize that participants in the group yoga will have greater improvements in neural network integrity. We also expect to see decreased task-dependent brain activity in the yoga group, which would suggest improved neural efficiency after yoga.

Finally, we expect that yoga will have a significantly greater impact on cognitive function and quality of life. A recent meta-analysis showed yoga interventions improve cognition and quality of life in individuals with TBI (Acabchuk et al., 2021). Although this study did not include individuals with acquired brain injuries, we anticipate similar findings in our population.

In summary, we hypothesize that our protocol will elicit improvements in both groups, particularly on balance performance. However, given prior literature – mostly conducted with healthy populations – we predict that the unique features of yoga will have a significantly greater impact on ANS function, integrity of neural networks, task-dependent brain activity, cognition and quality of life.

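### Functional networks, white-matter tracts and metrics are to be chosen in the light of behavioural findings, with no requirement to choose before results are seen by arm, which risks inflated type I error

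*Protocol article*

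**What the plan says.** Section 2.14.1 (functional connectivity) states "This analysis plan will be guided by findings from behavioral data and completed in SPM 12". It plans contrasts corrected for the false discovery rate (FDR), within and between groups and for interactions. The targets are described only as "specific neural networks (e.g., motor network", with no list. The tests over which the FDR is controlled are not defined.

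Section 2.14.2 (structural integrity) states "This analysis plan will also be guided by findings from behavioral data using contrasts"; the targets are differences "in structural integrity of specific WM tracts". It names no multiplicity correction.

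Section 2.9.2.2 does name regions: "we extract mean MWF values from regions representing the major association, projection, and commissural fibers". Those named are whole white matter, genu, body, splenium, prefrontal white matter, cingulum, corticospinal tract and uncinate. Myelin water fraction (MWF) is the only metric extracted there, but the processing in 2.9.2.1 also yields FA, ICVF and FISO. Section 2.14.2 does not say which regions and metrics will be tested.

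Section 4.1.2 states "we hypothesize that participants in the group yoga will have greater improvements in neural network integrity". Its background example is the default mode network, whereas the example in 2.14.1 is the motor network.

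**The concern.** This is a stated rule, not a detail left for a fuller plan. A list fixed in advance would replace the rule, not complete it. The other quantitative secondary outcomes carry no such rule: the fNIRS regions, cognition tests and quality-of-life measure are all named.

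The choice could be made with results by arm in view. Under 2.7 the PI learns the allocation once the follow-up assessments are done and scored. Under 2.12 the PI also looks over the outcome data after the first cohort's follow-up visits. The imaging targets need not be settled before either point.

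What is at stake is how a positive imaging result reads. Imaging is there to show what lies behind functional gains. A network tested because a related behaviour happened to differ between arms gives less independent support than its p-value suggests. The rule can also lose information: the Introduction reports a feasibility study with signs of better brain function where balance had not measurably improved, so selection by behaviour could drop a network that did change.

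**Working it through.** The documents give no figure for this point, so there is none to reproduce. The check asks how far selection on behaviour, as 2.14.1 and 2.14.2 describe, moves the error rate of an imaging test.

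**Inputs**
- Planned enrolment 36 (2.5); 36 / 2 = 18 per arm, assuming equal arms.
- Alpha 0.05, two-sided. The level is stated in 2.5 for balance; its use for imaging and two-sidedness are assumed.
- Number of candidates K: not given; 3, 5 and 9 assumed.
- Correlation rho between a behavioural change and the change in its matched network or tract: not given; 0 to 0.9 assumed. The Introduction theorises that functional gains rest on brain changes, so a value above 0 is plausible.

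**Model.** There are K mutually independent behavioural domains, each matched to one imaging target, with imaging change = rho × behavioural change + √(1 − rho²) × independent noise. No imaging effect exists. The target matched to the domain with the largest between-arm |t| is tested alone by a t-test on between-arm change. Each setting has 40,000 replicates, so the simulation standard error is √(0.05 × 0.95 / 40,000) = 0.001 near 0.05 and √(0.299 × 0.701 / 40,000) = 0.002 at the largest value.

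**Result, no true effect anywhere**

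| K | rho 0 | rho 0.3 | rho 0.5 | rho 0.7 | rho 0.9 | Ceiling 1 − 0.95^K |
|---|---|---|---|---|---|---|
| 3 | 0.050 | 0.060 | 0.079 | 0.102 | 0.135 | 0.143 |
| 5 | 0.050 | 0.068 | 0.099 | 0.140 | 0.201 | 0.226 |
| 9 | 0.051 | 0.075 | 0.123 | 0.192 | 0.299 | 0.370 |

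The last column is the rate if the best imaging result itself were picked from K independent ones. The protocol does not describe that practice, so the column is only a bound.

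**One behavioural effect real** (d = 1 in one domain, K = 5, still no imaging effect). The choice then depends less on chance, and the rate is 0.051 at rho 0, 0.056 at rho 0.5 and 0.077 at rho 0.9.

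**Fixed list.** With all K targets tested and Benjamini-Hochberg applied over all of them, the chance of any false positive with no true effect is 0.048 to 0.052 in every setting of the table.

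**The case against.** These are secondary outcomes of a pilot trial. The Introduction gives the imaging a mechanistic purpose, and letting behaviour direct a mechanistic question is reasonable. That stands, and it is why behaviour-led analyses should be kept. It does not justify reading them as tests of the directional hypothesis in 4.1.2. Behavioural data could also mean the earlier feasibility studies. The future tense makes this less natural, and if it were so the networks could be named now.

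Several stronger readings are tempting but not supported:
- *The FDR correction covers only the chosen networks.* The article does not define the FDR family, so this is an inference. For tracts no correction is named, so the argument cannot be made there at all.
- *The imaging tests are biased.* Selection is on behaviour, not on the imaging result. With uncorrelated changes the rate stays at 0.05.
- *The error is 1 − 0.95^K.* That is the ceiling for picking on imaging results.
- *All imaging outcomes and all tracts are open.* The fNIRS regions are fixed in 2.9.2.3, and 2.9.2.2 lists the MWF regions. What remains open is which networks, which of the listed regions and which metrics.
- *The imaging hypotheses are declared confirmatory.* Section 4.1.2 is directional but does not use that word.
- *The PI will choose the networks unmasked.* Sections 2.7 and 2.12 do not say who chooses or when. They only leave it possible.

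**Conclusion.** The point holds as a risk of inflated type I error in the connectivity and tract analyses. Over 3 to 9 candidates the simulated rate at nominal 0.05 is about 0.05 at rho 0, 0.079 to 0.123 at rho 0.5 and 0.135 to 0.299 at rho 0.9. With one real behavioural effect and five candidates it is at most 0.077 over the correlations tried. The size for this trial cannot be derived, because neither rho nor the number of candidates is given.

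The figures assume 18 per arm, one matched target per behavioural domain, a single target tested, and selection on the between-arm difference in behaviour. If the choice followed the change pooled over two equal arms, the risk would fall mainly on the within-subject contrasts, not on group-by-time.

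The conclusions on balance and autonomic function are untouched.

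**What to change.** Amend 2.14.1 and 2.14.2 so that, before any behavioural data are viewed by arm, including at the review after the first cohort, the plan fixes:
- the networks, for example the motor and default mode networks that the article mentions (as examples only, so the team must confirm them);
- the tract regions, taken from 2.9.2.2;
- the structural metrics to be tested among MWF, FA, ICVF and FISO. A list of regions alone would leave this choice open.

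Test group-by-time in every listed target, with FDR over the whole fixed set, separately for connectivity and for structure. Keep any analysis prompted by behavioural findings, labelled exploratory. If first-cohort results have already been seen by arm, say so and date the list.

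The cost is a few sentences and a somewhat stricter threshold, because more targets are counted. With two networks the smallest p-value must reach 0.05 / 2 = 0.025 if it alone is to pass Benjamini-Hochberg. With all eight named regions and four metrics (8 × 4 = 32 tests) it must reach 0.05 / 32 = 0.0016. A shorter structural list chosen in advance eases this. No analysis is lost.
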